#### Qualitative component

After completion of the intervention, 15–20 family caregivers who have received the intervention will be purposively selected for in-depth interviews. All the SCPs delivering the intervention will also be interviewed about their experience of delivering the intervention.

### The intervention

This study will assess the effectiveness of an intervention delivered via a mobile application by SCPs in reducing caregiving burden and depressive symptoms, and improving quality of life of family caregivers of persons with dementia by improving their caregiving competence.

#### Educational component of the intervention

The educational component of the intervention will be delivered by SCPs in Sweden via a mobile app. The intervention will be delivered in 10 sessions with specific topics for each session and which is based on World Health Organization’s recommendation of support for family caregivers. The topics include an introduction to dementia, being a caregiver, mental strategies and mind-set, activities, diet and sleep, and where to find resources in the community. The family caregiver will receive a booklet, presenting each topic and a minor task which will be followed up in the next session with the SCP. One of the 10 sessions will be kept as an open choice allowing the family caregiver to freely address any topic pertinent to their unique situation. The content of the intervention will be refined based on consultative workshops with stakeholders including SCPs, immigrant family caregivers of PWD, older persons of immigrant background and experts.

In addition to SCPs delivering the intervention through the chat feature on a mobile application, other features of the app will include:

***Interaction with community workers***: Using the chat feature, family caregivers will be able to communicate directly with the SCPs on a one-on-one basis throughout the 10-week intervention period.***Relevant services***: Collection of weblinks of relevant services in their communities will be available.***Peer support***: The family caregivers will be able to chat with their peers, i.e., other family caregivers of persons with dementia, at the time of their preference.***Wellbeing***: Mindfulness exercises will be available for the family caregivers.***Diary***: The family caregivers will be able to write down personal notes and reflections.

#### Training of SCPs

All SCPs will receive a short training introducing them to the mobile app and familiarizing them with contents of the intervention. The training will be provided by a team of two nurses specialized in dementia care and care of older persons with expertise in training nurses in dementia care at university level education.

The research team and the SCPs will meet virtually at least twice during every cycle of the 10-week long intervention period to discuss and calibrate their approach in their interaction with family caregivers, and to discuss possible challenges in delivery of the intervention. This will enhance the fidelity of the intervention by ensuring that the intervention is implemented as intended.

### Evaluation of the intervention & data collection

#### Quantitative assessment of outcomes

The quantitative data will be collected to capture the impact of the intervention implemented by SCPs on the outcome measures caregiver burden [30], depressive symptoms [31], quality of life [32] and caregiving competence [33] of family caregivers.

Background information of the family caregivers such as age, sex, social network, relationship with the PWD, living arrangement will be included. Outcomes will be measured in both the intervention and wait list control groups at baseline prior to delivery of intervention (T1), after completion of the 10-week intervention in the intervention group (T2), and after completion of the 10-week intervention in the wait list control group (T3).

#### Qualitative assessment of stakeholders’ experiences and insights

In-depth interviews will be conducted with the two groups of key stakeholders of the project for three-fold purpose: (i) family caregivers to get an understanding of their experiences of receiving support from the SCPs through the mobile app including areas of improvement; (ii) SCPs to evaluate delivery of the intervention via the mobile app in terms of use and practicality of the app, and particularly in combination to their regular responsibilities; and (iii) Acceptability by SCPs and family caregivers in providing and receiving support through a mobile application. The interviews will be undertaken using a semi-structured interview guide and take place shortly after the 10-week intervention cycle. Even chat data of communication between the family caregivers and SCPs will be qualitatively analyzed to identify themes meaningful for future caregiving to family caregivers of minority ethnic groups by professionals.

A data monitoring committee will not be needed, as the included participants (family caregivers), are at a low risk of unintended harm.

#### Assessment of logged data

Usage of the app will be assessed by analytics information, logged on backend system, on the features of the mobile application described above.

The mHealth evidence reporting and assessment (mERA) checklist [25] will be followed to report on proposed intervention using mobile devices. The checklist of 16 items includes information on, for example, population level infrastructure, technology platform, intervention content, content testing, user feedback, fidelity of the intervention, etc.

The usability of the mobile app, through which the intervention is delivered, will be assessed by the following parameters:

1) *Usage* of the mobile app as indicated below (Derived from app data):

Frequency of communication between family caregivers and the SCP through chat.Use of collection of weblinks of relevant services.Frequency of use of peer support through contact between fellow family caregivers.Use of mindfulness exercises.

2) User Experience in terms of *satisfaction* level of the interface of the mobile app and the content of the intervention (Interviews with family caregivers and SCPs).

3) User Experience in terms of *ease* of usage of the mobile application (Interviews with family caregivers and SCPs).

### Data analysis

#### Outcome analysis

The outcome analysis of the intervention will include quantitative assessment of family caregivers’ caregiving competence, reduction in caregiver burden and depression, and improvement in quality of life.The *quantitative* data will be analyzed to describe and compare differences in caregiver competence, caregiver burden, depressive symptoms and quality of life amongst family caregivers between the baseline and post-intervention phases. Impact of the intervention on the odds of improving the specified outcomes will be assessed by regression analyses. All data will be analyzed using Statistical Package for Social Scientists. As neither blinding of participants, SCP’s or researchers are possible, pseudo anonymized data will be sent to a data analyst who will initiate the analysis or data.

The *logged* data on the mobile application will be quantitatively analyzed for associations between use of the different features of mobile app and the outcome measures.

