### Recruitment of participants

#### Quantitative component

Sample size calculation of family caregivers is based on the primary outcome caregiver burden assessed by Zarit Burden Interview [30]. Assuming an effect size of 0.70, alpha 0.05, power 0.80, and 25% refusal or drop-out rate, the required sample size will be 44 family caregivers each in intervention group and wait list control group, totaling a sample size of 88. Recruitment of family caregivers will be done in multiple ways. The SCPs of the municipalities selected for the study will announce to all in the network of the family caregivers of PWD, as defined above, who are in their catchment area. Announcement about the project and invitation to join the study will be published in the local newspaper if necessary. Cultural and community organizations of different ethnic minority groups will also be reached out with information on the project. Participants will be randomized 1:1. To ensure allocation concealment, a sealed opaque envelope containing 88 small pieces of paper with numbers 1–88 written on it. Of these, 44 will be marked with “I” to indicate intervention group and another 44 with “C” to indicate control group. Once a participant is enrolled in the study, a person outside the research group will randomly pick a piece of paper from the envelope to indicate if the enrolled participant will belong to the intervention group or the wait list control group.

After inclusion, the SCP will contact a designated member of the research team who will draw a sealed envelope which will decide the allocation to either control or intervention group. A SCP selected for the study will be responsible for 5–7 family caregivers at a time for delivering the intervention. Those family caregivers not selected in the initial intervention group, i.e., those in the wait list control group, will continue to receive the standard support. Recruitment of study participants is expected to begin in August 2024.

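### The outcome analysis is framed as change from T1 and does not say that the T1 score enters the between-group comparison

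*Protocol article*

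**What the plan says.** Under Data analysis, the Outcome analysis section of the protocol article commits to two things. The data will be analysed to describe and "compare differences in caregiver competence, caregiver burden, depressive symptoms and quality of life amongst family caregivers between the baseline and post-intervention phases". Then: "Impact of the intervention on the odds of improving the specified outcomes will be assessed by regression analyses". The regression's covariates are not listed, and what counts as improving is not defined.

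The Study design section adds that the effect will be examined across arms and inside each arm over time. It names no model.

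The T1 score will be available. The Quantitative assessment of outcomes section states: "Outcomes will be measured in both the intervention and wait list control groups at baseline prior to delivery of intervention (T1"), followed by T2 after the intervention arm's 10 weeks and T3 after the control arm's.

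The sample size, in the Quantitative component of Recruitment of participants, concerns one outcome: "Sample size calculation of family caregivers is based on the primary outcome caregiver burden assessed by Zarit Burden Interview". Its inputs are: "Assuming an effect size of 0.70, alpha 0.05, power 0.80, and 25% refusal or drop-out rate". It does not mention a T1–T2 correlation or say which SD standardises the 0.70.

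**The concern.** When a caregiver is scored by change from T1, the result depends on where that caregiver started. People with high burden at T1 tend to fall by more than people with low burden, through regression to the mean. This holds whenever r < SD(T1)/SD(T2), which with equal SDs means any r below 1. The arm that by chance starts worse will therefore tend to look as if it improved more. The allocation is a simple 1:1 draw with no stratification on baseline burden stated, and the planned number of evaluable caregivers is small, so imbalances of some size should be expected.

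A change score also subtracts the whole of T1, where a regression would subtract only the part that predicts T2. That adds noise. What is at stake is how one realised trial is interpreted and how wide its interval is. The average of the estimate over repeated randomisations is not affected.

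**Working it through.** **Inputs from the protocol article (Quantitative component).** Effect size 0.70, alpha 0.05, power 0.80, "25% refusal or drop-out rate", 44 per arm, and "Participants will be randomized 1:1".

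**Assumed, because not given.** T1–T2 correlation r from 0.3 to 0.8; equal SDs at T1 and T2; a two-sided test; independent caregivers.

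**1. The plan's own figure.** n per arm = 2(1.960 + 0.842)²/0.70² = 32.04, so 33. Inflated for loss: 33/0.75 = 44 per arm, 88 in total. This matches the article. A one-sided test gives 26, or 35 after inflation, and does not match. The 88 therefore reproduces as a plain two-group comparison that assumes no gain from T1, with 33 evaluable per arm.

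**2. Variance of the effect, relative to an unadjusted T2 comparison.**
- Change from T1: 2(1−r)
- T2 adjusted for T1: 1−r² = (1−r)(1+r)
- Ratio, change to adjusted: 2/(1+r)

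**3. Power at 33 per arm, 0.70 in T2-score SDs.** Normal approximation: Φ(0.70/√(2v/33) − 1.96), with v from step 2.

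| r | variance ratio | change score | T1-adjusted |
|---|---|---|---|
| 0.3 | 1.54 | 67% | 85% |
| 0.4 | 1.43 | 74% | 87% |
| 0.5 | 1.33 | 81% | 91% |
| 0.6 | 1.25 | 89% | 94% |
| 0.7 | 1.18 | 96% | 98% |
| 0.8 | 1.11 | 99% | over 99% |

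Noncentral-t values are about one point lower (for example 66% and 84% at r = 0.3).

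**4. Power if 0.70 is instead in change-score SDs.** The unadjusted change comparison has 81% whatever r is. T1 adjustment gives 94% at r = 0.3, 91% at 0.5, 87% at 0.7 and 85% at 0.8.

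**5. Carry-over of imbalance.** The standard error of the T1 difference is √(2/33) = 0.246 SD, so an imbalance above 0.25 SD has about a 31% chance. The change-score estimate moves by (1−r)b in favour of the arm that starts worse. For b = 0.25 SD the shift is 0.125, 0.10 and 0.075 SD at r = 0.5, 0.6 and 0.7. For an imbalance of 1.96 standard errors (0.48 SD) at r = 0.5 it is 0.24 SD, about a third of 0.70.

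**6. Simulation check (5,000 trials, 33 per arm, r = 0.5, 0.6, 0.7).** The slope of the change-score estimate on the T1 difference was −0.47, −0.40 and −0.30. For the T1-adjusted estimate it was about 0. Both estimators averaged about 0.70. Power for change versus adjusted was 81% vs 89%, 88% vs 94% and 95% vs 97%.

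**The case against.** The strongest objection is that non-adjustment is read from silence. One might infer that the plan rules out T1 adjustment. The text does not support that: the second analysis is a regression with no covariates listed and none excluded, and the Study design wording would fit a repeated-measures model that uses T1. A journal article commonly leaves the covariate list to a fuller plan, and a bare missing list would be no finding. This stands against any claim that T1 is omitted. It does not remove the narrower point, because the article does choose how the effect is expressed, as differences from baseline and odds of improving, and a T1-adjusted T2 score is not among the analyses it names.

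Two other strong readings also fail. One is that the estimate is biased. It is not: over randomisations it is centred on the true effect, and the shift exists only given the imbalance that occurred. The 0.24 SD example needs an imbalance exceeded in only 5% of trials. The other is that the trial is underpowered. That requires both r below 0.5 and 0.70 in T2-score SDs, and the article gives neither r nor the SD.

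It is also fair to say that the power figures above are for a continuous change score and not for the odds regression. If improving means any change in the right direction, with no mean change in controls and normal scores, that analysis has about 59%, 68% and 79% power at r = 0.5, 0.6 and 0.7. Dichotomising therefore costs more than omitting T1. It is a separate matter: the T1 question remains when the change is kept continuous.

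**Conclusion.** The point holds as a free improvement and a needed clarification. The Outcome analysis section expresses the effect on a change-from-T1 scale and does not say that T1 enters the between-group comparison. If it does not enter, the variance of a continuous comparison is 1.11 to 1.54 times what it need be for r from 0.8 down to 0.3, and a share (1−r) of any chance baseline imbalance carries into the estimate. T1 adjustment was at least as precise at every r examined, whichever SD the 0.70 refers to.

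These sizes rest on an assumed r, equal SDs, 33 evaluable per arm and independent caregivers. Planned power is not shown to be lost, since the 88 counted on no help from T1. Outside the case of r below 0.5 with 0.70 in T2-score SDs, the cost is forgone precision.

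**What to change.** In the Outcome analysis section, make the main between-group analysis of each outcome a linear regression of the continuous T2 score on randomised arm, with that outcome's own T1 score as a covariate. Report the adjusted mean difference with its 95% interval. Use standard errors that allow for caregivers who share a person with dementia, since the Study participants and inclusion criteria section permits several per person and places them in the same arm. Keep changes from T1 and the odds of improving as descriptive or secondary results.

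The cost is a change of wording and one degree of freedom for the covariate. T1 is already collected in both arms, so no visit, measurement or participant is added. Fixing this before data are seen also removes a later choice between adjusted and unadjusted results.

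### The sample size rests on a difference in mean burden score, but the only effect measure named for the intervention is the odds of improving, so the stated 0.80 power is not tied to the named analysis

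*Protocol article*

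**What the plan says.** Under Recruitment of participants, Quantitative component, the article states: "Sample size calculation of family caregivers is based on the primary outcome caregiver burden assessed by Zarit Burden Interview". The inputs are given as "Assuming an effect size of 0.70, alpha 0.05, power 0.80, and 25% refusal or drop-out rate", and the result is that "the required sample size will be 44 family caregivers each in intervention group and wait list control group, totaling a sample size of 88". Allocation is equal: "Participants will be randomized 1:1".

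Under Data analysis, Outcome analysis, two sentences bear on the effect. The first is descriptive: "The *quantitative* data will be analyzed to describe and compare differences in caregiver competence, caregiver burden, depressive symptoms and quality of life amongst family caregivers", taken between baseline and the post-intervention phases. The second says how the effect of the intervention is judged: "Impact of the intervention on the odds of improving the specified outcomes will be assessed by regression analyses".

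The Study design section adds, in general terms, that effects will be examined both across and inside the groups over time. No model is named there.

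**The concern.** A sample size calculation holds for one outcome and one comparison. This one is built on a difference in means of a continuous score. The analysis sentence expresses the effect as odds of improving, which requires each caregiver to be classed as improved or not. Splitting a continuous score in two discards information, so the same number of caregivers supports a weaker test. An odds ratio also cannot be read directly against the planned effect of 0.70.

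At stake is whether a trial of 88 caregivers, a quarter of whom may not contribute data, keeps its planned chance of detecting the effect it was sized for. An analysis plan that follows the article's sentence would carry the mismatch forward.

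**Working it through.** **Inputs from the article:** effect size 0.70, alpha 0.05, power 0.80, 25% refusal or drop-out, 1:1 allocation, 44 per arm. The article does not name the type of effect size or the sidedness of alpha.

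**Step 1: reproduce the stated size.** For two means, two-sided:

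n = 2 × (1.960 + 0.842)² / 0.70² = 32.04, rounded up to 33 per arm.

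33 / (1 − 0.25) = 44 per arm, 88 in total. This matches exactly. The two-sample t-test at 33 per arm has power 0.7997. A one-sided calculation gives 26, then 35 per arm, which does not match. The trial is therefore sized on a two-sided comparison of means with a standardised difference of 0.70.

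**Step 2: power if the same data are classed as improved/not improved.** Assumptions, none given in the documents:
- normal scores with equal SD in both arms;
- a 0.70 SD difference in the T2 score;
- T1–T2 correlation r;
- improvement defined by a cut on the change score at which a proportion pc of controls improve.

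Formulas:
- Effect on the change score: d = 0.70 / √(2(1 − r)).
- Proportion improving in the intervention arm: pt = Φ(Φ⁻¹(pc) + d).
- Power = Φ[(pt − pc − 1.96·se₀) / se₁], where se₀ uses the pooled proportion and se₁ the separate ones, with 33 per arm.

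Example with r = 0.5 and pc = 0.50:
- d = 0.70 / √1 = 0.70 and pt = Φ(0.70) = 0.758.
- The pooled proportion is 0.629, so se₀ = √(0.629 × 0.371 × 2/33) = 0.119.
- se₁ = √((0.25 + 0.758 × 0.242)/33) = 0.115.
- Power = Φ[(0.258 − 1.96 × 0.119)/0.115] ≈ 0.59, carrying unrounded values.

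**Step 3: power of ANCOVA on the same data.** The effect in residual SD units is 0.70 / √(1 − r²). At r = 0.5 this is 0.70 / √0.75 = 0.81, and the t-test power at 33 per arm is 0.90.

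**Step 4: range over the assumed correlation** (33 per arm, two-sided 0.05, pc from 20% to 60%):

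| Assumed r | Improved/not improved, unadjusted | ANCOVA |
|---|---|---|
| 0.3 | 0.43–0.47 | 0.84 |
| 0.5 | 0.54–0.61 | 0.90 |
| 0.6 | 0.63–0.70 | 0.94 |
| 0.7 | 0.73–0.82 | 0.975 |
| 0.8 | 0.86–0.95 | over 0.99 |

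At r = 0.5, restoring 0.80 power for the binary outcome would take 52–60 evaluable caregivers per arm, depending on the cut. That is 70–80 randomised per arm after division by 0.75.

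**The case against.** The strongest reply is that the article does not rule out a continuous comparison. The sentence before the one on odds speaks of comparing differences in the outcomes, and the Study design section promises comparisons across groups and over time. Either could be the comparison of means that the sample size supports. This stands in part: it would be wrong to say that the article commits itself to a binary analysis alone. But neither sentence names a between-arm model, and the only sentence about the impact of the intervention uses odds.

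A second reply is that the power loss depends on unknowns. This stands. A reader might infer that power is simply about 0.6, so that a true effect would be missed 4 times in 10. That is the case at r = 0.5 only. At r = 0.7 the binary comparison is close to 0.80, and at r = 0.8 it exceeds it. The article also speaks of regression, which may be adjusted: in simulation (3,000 runs), logistic regression of any improvement on arm and T1 score reached 0.67 at r = 0.5 and 0.83 at r = 0.7, against 0.60 and 0.80 unadjusted. These remain below ANCOVA. The word odds could also fit an ordinal model.

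Two further inferences are tempting but unsupported. One is that the T1 score is left out as a covariate: the article lists no covariates, so it neither includes nor excludes T1. The other is that the missing threshold will lead to a search over cut-points and inflated false positives: no sentence provides for such a search, and a condensed article commonly leaves the threshold to the full protocol or analysis plan.

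**Conclusion.** The mismatch holds. The sample size is that of a comparison of mean burden scores, while the one effect measure named is the odds of improving. The 0.80 power is therefore not attached to the analysis as named.

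Over assumed correlations of 0.3 to 0.8, unadjusted power for the binary comparison runs from 0.43 to 0.95. It is below 0.80 throughout for correlations up to 0.6, straddles it at 0.7 and is above it at 0.8. A shortfall against plan is likely but not established. The firmer result is that the binary comparison has less power than ANCOVA at every correlation tried. The figures rest on 33 evaluable per arm, normal scores with equal SD, a 0.70 SD effect at T2 and 20–60% of controls improving.

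**What to change.** State in the Outcome analysis section that the primary analysis is the between-arm difference in mean Zarit burden score at T2, with a 95% confidence interval, from a linear regression or mixed model adjusted for the T1 score. Keep the odds of improving as a supportive analysis, with the threshold for improvement fixed before the data are seen.

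The cost is protocol wording only: T1 and T2 scores are already to be collected in both arms, and no further caregivers are needed. If the odds of improving is meant to be primary, the sample size should instead be recalculated for that outcome, with the threshold and the assumed proportions stated.
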